| Difficult biliary stone(s)  – any of: 
 
• One or more stone(s) <math>\geq 15</math> mm
 
• Barrel or other unusual shape
 
• Multiple (4 or more stones)
 
• Impacted stone(s)
 
• Intrahepatic or cystic duct stone(s)
 
• Stricture below stone(s)
 
 | Extraction of stone(s)

OR

CBD clearance based on absence of filling defects on occlusion cholangiogram

OR

Stenting of CBD as part of future plan to clear duct                                                                                        |
| Biliary stricture (benign or malignant)                                                                                                                                                                                                                                                                                                                 | Successful placement of stent with proximal margin proximal to stricture

OR

Successful dilatation of stricture                                                                                                                                                      |
| Cholangioscopy or pancreatoscopy                                                                                                                                                                                                                                                                                                                        | Successful cholangioscopic or pancreatoscopic visualization of area of interest                                                                                                                                                                                                   |
| Chronic pancreatitis, pancreatic stone(s) and/or pancreatic stricture(s)                                                                                                                                                                                                                                                                                | Successful cannulation of main pancreatic duct (PD)

AND AT LEAST 1 OF:

Pancreatic sphincterotomy
Stenting or dilatation of PD
Extraction of PD stone(s)                                                                                                       |

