| Inability to achieve an en-face view of the papilla of interest due to a luminal stricture                                                                                                                                      |
| Inability to cannulate duct of interest                                                                                                                                                                                         |
| Inability to perform sphincterotomy when necessary                                                                                                                                                                              |
| Inability to clear duct of interest                                                                                                                                                                                             |
| Inability to place stent proximal to area of interest                                                                                                                                                                           |
| Inability to remove or exchange stent                                                                                                                                                                                           |
| Inability to achieve hemostasis endoscopically                                                                                                                                                                                  |
| Inability to successfully load, exchange or remove devices necessary for the completion of the procedure                                                                                                                        |
| Inability to safely complete procedure due to issues with sedation*                                                                                                                                                             |
| *If this is the only reason for technical failure, the patient will be excluded from final analysis                                                                                                                             |

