## **8. Study Period and Sequences**

### **8.1. Index Procedure**

Consecutive patients undergoing ERCP will be flagged as potentially eligible for study participation. On the day of the procedure, the patient will be approached by a research assistant (RA), who will explain the study, confirm eligibility, and answer any potential questions. If the patient agrees to participate, the relevant informed consent form is signed and witnessed. If the patient decides not to participate, the ERCP proceeds as per the usual standard of care, with or

without the use of DEC as per the endoscopist's discretion (and the sequence that follows does not apply).

1. The RA collects any relevant patient-related and pre-procedural data through combination of direct patient interview and review of the medical records.
2. The patient is randomized to one of the two study arms.
3. The patient enters the endoscopy/fluoroscopy room and the procedure commences.
4. During the ERCP procedure, relevant peri-procedural data are recorded by the RA by direct observation, and/or, if necessary, in consultation with the procedural physician(s) and/or nurse(s).
5. After the procedure is complete, the patient is moved to the recovery room for observation. Depending on their disposition and the course of the procedure, observation times and protocols differ. During this stage, the RA collects any relevant post-procedural data, and any missing pre- or peri-procedural data.
6. Any peri- or immediate post-procedural adverse event(s) is/are recorded.
7. The patient is examined by the endoscopist prior to discharge and provided with written post-procedure information, including a phone number to call in the event of any issues.
8. The RA meets with the patient prior to their discharge from the unit to answer any final potential questions.

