| cbd_or_pd        | targetted duct for cannulation                                                  | 0 = common bile duct; 1 = pancreatic duct                                                                                                                                                                                                                                                             |
| scope_position   | scope position during ERCP                                                      | 1 = short; 2 = long                                                                                                                                                                                                                                                                                   |
| pre_cut          | pre-cut sphincterotomy performed (includes trans-pancreatic or supra-papillary) | 0 = no; 1 = yes                                                                                                                                                                                                                                                                                       |
| nk_papillotomy   | needle knife papillotomy performed                                              | 0 = no; 1 = yes                                                                                                                                                                                                                                                                                       |
| cbd_cannulation  | CBD cannulation achieved (only calculate among patients where cbd_or_pd = 0)    | 0 = no; 1 = yes                                                                                                                                                                                                                                                                                       |
| cannulation_time | cannulation time (only calculate among patients where cbd_cannulation = 1)      | (continuous)                                                                                                                                                                                                                                                                                          |

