| sphinct          | formal sphincterotomy performed with sphincterotome                             | 0 = no; 1 = yes                                                                                                                                                                                                                                                                                       |
| balloon_sphinct  | balloon sphincteroplasty performed                                              | 0 = no; 1 = yes                                                                                                                                                                                                                                                                                       |
| cbd_stones       | CBD stones found                                                                | 0 = no; 1 = yes                                                                                                                                                                                                                                                                                       |

|                 |                                                               |                      |
|-----------------|---------------------------------------------------------------|----------------------|
| cbd_stricture   | CBD stricture found                                           | 0 = no; 1 = yes      |
| leak            | bile leak found                                               | 0 = no; 1 = yes      |
| cholangioscopy  | cholangioscopy performed                                      | 0 = no; 1 = yes      |
| biliary_stent   | biliary stent placed                                          | 0 = no; 1 = yes      |
| panc_stent      | pancreatic stent placed                                       | 0 = no; 1 = yes      |
| proc_time       | procedure time (from intubation to extubation)                | (continuous)         |
| gen_anesth      | general anesthesia or monitored anesthesia care performed     | 0 = no; 1 = yes      |
| midazolam       | amount of midazolam given (only calculate for gen_anesth = 0) | 0 = no; 1 = yes      |
| fentanyl        | amount of midazolam given (only calculate for gen_anesth = 0) | (continuous)         |
| glucagon        | amount of midazolam given (only calculate for gen_anesth = 0) | (continuous)         |

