### C) ANALYSIS

Two-tailed Fisher's exact tests and chi-squared tests will be used to compare proportions. Outcomes will be compared between groups in an intention-to-treat analysis without adjustment. Comparisons will be reported using relative risks (RRs) and numbers needed to treat (NNTs) along with their respective 95% confidence intervals (CIs).

*Post hoc* subgroup analyses will be performed on sex (female or male), age (<65 or ≥65 years), study site (Calgary or Kingston), procedural complexity (1-2 or 3-4), papilla status (native

papilla or prior sphincterotomy), disposition (inpatient or outpatient), biliary stent placement (present or none), and indication (suspected or confirmed malignancy or all others). All statistical analyses will be performed using RStudio version 1.2.1335 (Integrated Development Environment for R, Boston, USA).

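### The biliary-stent subgroup splits patients on something decided during the ERCP, and for technical success it partly splits them on the outcome itself

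*Supplement*

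**What the plan says.** SAP section C plans eight subgroup factors, labelled post hoc. One of them is "biliary stent placement (present or none". Section D plans a forest plot of the subgroups. Neither section says which outcome the subgroups are run on.

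The only matching entry in the data dictionary (SAP section B) is `biliary_stent`, described as "biliary stent placed". The dictionary has no field for a stent already in situ or for an intended stent.

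Protocol section 8.1 (two-centre version) fixes the order of events. At step 2, "The patient is randomized to one of the two study arms"; the procedure starts at step 3.

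Protocol section 7.1.1, Table 1, counts a stent towards technical success in two rows:
- Biliary stricture: "Successful placement of stent with proximal margin proximal to stricture", with successful dilatation as the alternative.
- Difficult stones: "Stenting of CBD as part of future plan to clear duct", as one of three alternatives.

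Table 2 lists "Inability to place stent proximal to area of interest" and "Inability to cannulate duct of interest" among the reasons for technical failure.

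The dictionary also restricts one time variable: "cannulation time (only calculate among patients where cbd_cannulation = 1".

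**The concern.** A subgroup comparison keeps the protection of randomisation only if the factor is settled before the assigned scope can affect it. Whether a stent was placed is settled while that scope is in use. If one scope makes stenting harder, patients in that arm move from the stent stratum to the no-stent stratum, and the two arms within a stratum are no longer comparable.

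For technical success there is a second problem. In two indications the event that puts a patient in the stent stratum is also an event that makes the procedure a success, and failure to achieve it is a listed reason for failure. The stratum then carries part of the outcome. A forest plot could suggest that the disposable-cap scope performs equally well when a stent is placed and worse when none is, with that contrast produced by the sorting alone.

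Cannulation time raises a smaller version of the same issue. Failed cannulations, probably the longest attempts, are left out, and an arm with more failures loses more of them.

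**Working it through.** **Plan's own figure.** Protocol section 9.1 assumes 92% success in both arms, a 7-point margin, one-sided alpha 0.025 and 80% power.

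n per arm = (1.960 + 0.842)² × (2 × 0.92 × 0.08) / 0.07² = 7.849 × 0.1472 / 0.0049 = 235.8, so 236, as stated. The sample size is not in question.

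**Inputs for the illustration.**
- From the protocol: control success 92%. DEC success is set at 85%, so that the true difference equals the margin.
- Assumed, because the documents do not give them: share of patients needing a stent, s = 0.40; share of failures that are failed stent placements, h = 0.50; every placed stent counts as a success.

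**Formulas.** Let f be the failure rate in an arm.
- Stent placed: s − h·f, with success 100%.
- No stent: (1 − s) + h·f, with success 1 − f / [(1 − s) + h·f].

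**Results.**

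| | Control (f = 0.08) | DEC (f = 0.15) | Difference |
|---|---|---|---|
| Share with stent placed | 0.40 − 0.04 = 36.0% | 0.40 − 0.075 = 32.5% | 3.5 points |
| Success, stent present | 100% | 100% | 0 |
| Success, none | 1 − 0.08/0.64 = 87.5% | 1 − 0.15/0.675 = 77.8% | 9.7 points |
| Success, overall | 92% | 85% | 7 points |

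**Comparison with a split on need, fixed before the procedure.** The same patients give:
- Needing a stent: control 1 − 0.04/0.40 = 90.0%, DEC 1 − 0.075/0.40 = 81.25%; difference 8.75 points.
- Not needing one: control 1 − 0.04/0.60 = 93.3%, DEC 1 − 0.075/0.60 = 87.5%; difference 5.8 points.

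In this example the larger difference lies in the patients who need a stent. The split on stent placed shows zero in its stent stratum and puts the whole difference in the other.

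**Range.** With s from 0.30 to 0.50 and h from 0.25 to 1.00, the stent stratum stays at 0 and the no-stent difference runs from 7.4 to 12.5 points.

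**Relaxing the last assumption.** Keep s = 0.40 and h = 0.50, and let a further quarter of failures occur with a stent in place.
- Stent present: 1 − 0.02/0.36 = 94.4% v 1 − 0.0375/0.325 = 88.5%; difference 6.0 points.
- None: 1 − 0.06/0.64 = 90.6% v 1 − 0.1125/0.675 = 83.3%; difference 7.3 points.
- Needing a stent: 1 − 0.06/0.40 = 85.0% v 1 − 0.1125/0.40 = 71.9%; difference 13.1 points.
- Not needing one: 1 − 0.02/0.60 = 96.7% v 1 − 0.0375/0.60 = 93.75%; difference 2.9 points.

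The sizes change, but the stent-placed split still misstates where the difference lies.

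**No true difference.** If f and h are equal in the two arms, each stratum also shows no difference. In this model the split misplaces a real difference; it does not create one from nothing.

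**Cannulation time.** Assumed: lognormal times with log-scale SD 1, a median of 5 min in the better arm, and a common give-up time giving 96% v 89% cannulated. The 96% is the centre's native-papilla rate in section 9.1; the 89% is an assumption.
- Mean over all patients, had every attempt run to completion: 8.24 v 13.92 min, difference 5.7.
- Mean among successes: 6.64 v 9.22 min, difference 2.6.
- Median difference: 3.4 min over all patients, 2.6 min among successes.

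The gap narrows, and the slower arm remains the slower one.

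**The case against.** The strongest reply is that little depends on this subgroup. It is one of eight, all labelled post hoc. The main comparisons are unadjusted intention-to-treat, and neither they nor the sample sizes involve stent placement. That is correct and limits the weight of the point. The label, however, deals with timing and multiplicity. It does not make a post-randomisation split comparable between arms, and the SAP lists this factor beside genuine baseline ones such as sex, age and site without any caution.

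Second, the SAP names no outcome for the subgroups. If they are meant for contamination, stenting forms no part of that definition (section 7.1), and only the general post-randomisation objection is left. This stands.

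Third, Table 1 does not equate a stent with success. Strictures can succeed by dilatation. A stent counts there only if it reaches beyond the stricture. Ordinary stones need extraction or clearance, and several indications do not involve a biliary stent at all. A reader might infer that the stent stratum must show 100% success, or that the difference vanishes from both strata. The second would need a population of strictures only, without dilatation, whereas the trial enrols ERCP for any indication. The documents support partial overlap with the outcome and no more.

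Fourth, a reader might infer that success-only cannulation time would make the worse arm look faster. The calculation shows attenuation, not reversal. Cannulation time is not a secondary outcome in section 7.2, the SAP names tests only for proportions, and `cbd_cannulation` is available for all patients with a bile-duct target. That part is therefore minor.

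**Conclusion.** The concern holds for the biliary-stent subgroup. The factor arises after randomisation whatever the outcome. For technical success it is also partly outcome-defined, for strictures and difficult stones.

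Under the stated assumptions the strata show differences of 0 and 9.7 points when the overall difference is 7, with a range of 7.4 to 12.5 points in the no-stent stratum. These figures illustrate the mechanism and do not forecast the trial's result. They rest on an assumed need for stenting, an assumed mix of failures, a true difference equal to the margin, and every placed stent being a success.

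For contamination only the weaker objection applies. Nothing here bears on the primary comparisons or the sample sizes. Restricting cannulation time to successes understates slowness in an arm with more failures; it has not been shown to reverse the ranking.

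**What to change.** 1. Remove biliary stent placement from the subgroup list and the forest plot, or replace it with a factor fixed before the procedure. The dictionary's `indication` variable already has stricture and obstruction categories (codes 1, 3 and 4), which could be set against the rest. Use that variable and not the Table 1 row, because Table 1 lets a case move to the difficult-stone row on findings made during the ERCP.
2. State which outcome each subgroup analysis uses. If the stent split is kept for contamination, label it descriptive and non-randomised.
3. Report cannulation time beside the cannulation success rate in all patients with `cbd_or_pd` = 0. Then either rank failures as worst, which needs only `cbd_cannulation`, or label the success-only time descriptive. Censoring failures at the end of the attempt would need a time that the dictionary does not list for them.

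Cost: a change of SAP wording, with no new data for the options recommended here, and one subgroup fewer. A split on a stent already in situ would need a field that the dictionary does not contain, so `indication` is the cheaper substitute.

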#### **D) OUTPUTS**

1. Table comparing proportions of variables between study groups
2. Summary of RRs, ARRs, RRRs, NNTs, NNHs
3. Subgroup analyses and forest plot of subgroups
